## Abstract

**Background:**

SARS-CoV-2 infection is associated with a significant risk of hospitalisation, death, and prolonged impact on quality of life. Evaluation of new treatment options and optimising therapeutic management of people hospitalised with SARS-CoV-2 infection remains essential, but rapid changes in pandemic conditions and potential therapies have limited the utility of traditional approaches to randomised controlled trials.

**Methods:**

ASCOT ADAPT is an international, investigator-initiated, adaptive platform, randomised controlled trial of therapeutics for non-critically ill patients hospitalised with COVID-19. The study design is open label and pragmatic. Potential participants are hospitalised adults with PCR confirmed, symptomatic, SARS-CoV-2 infection, within 14 days of symptom onset. Domains include antiviral, antibody and anticoagulant interventions, with a composite primary outcome of 28-day mortality or progression to intensive-care level respiratory or haemodynamic support. Initial interventions include intravenous nafamostat and variable dose anticoagulation. A range of secondary endpoints, and substudies for specific domains and interventions are outlined.

**Discussion:**

This paper presents the trial protocol and management structure, including international governance, remote site monitoring and biobanking activities and provides commentary on ethical and pragmatic considerations in establishing the ASCOT ADAPT trial under pandemic conditions.

**Trial registration:**

Australian and New Zealand Clinical Trials Registry (ACTRN12620000445976) and ClinicalTrials.gov (NCT04483960).

**Supplementary Information:**

The online version contains supplementary material available at 10.1186/s13063-022-06929-y.

## Background

The development of COVID-19 vaccines with efficacy against both infection and severe disease is a welcome and remarkable development and key to pandemic control [1, 2]. Despite vaccine availability, optimising therapeutics for people hospitalised with COVID-19 remains essential as existing vaccines provide imperfect protection and because access to vaccines remains limited in many countries [3]. The emergence of SARS-Co-V variant strains associated with apparent differential vaccine efficacy is another reason why therapeutics will remain critical for the foreseeable future.

Initially, the ASCOT trial was developed as a 2 × 2 factorial trial of COVID-19 therapeutics [4]. This design was selected in the early COVID-19 pandemic period for relative simplicity and allowed the rapid establishment of a network of active trial sites across Australia and New Zealand. From the outset, however, it was intended that this be used as a forerunner to the development of ASCOT ADAptive Platform Trial (ADAPT), which is outlined in this report.

## Methods

Adaptive Platform Trials are an innovative trials methodology [5–7], which have been successfully operationalised by RECOVERY [8–10], SOLIDARITY [11], and REMAP-CAP [12, 13], arguably the clinical trials that have most advanced COVID-19 clinical therapeutics to date.

Conventional randomised controlled trials (RCT), at the time of design, make assumptions about plausible effect size, primary outcome incidence, and sample size; holding assumptions constant until trial completion. Adaptive trials incorporate pre-specified adaptation mechanisms, which allows their structure to evolve based on accruing evidence. Platform trials are adaptive trials that allow multiple questions to be evaluated simultaneously with the goal of identifying optimal treatments for a disease as efficiently as possible.

ASCOT ADAPT comprises the following critical components:A core master protocol with minimal, easily identified inclusion and exclusion criteria, specifying the key primary endpoint of 28-day mortality or need for intensive respiratory supportA number of parallel treatment domains, initially including antiviral, antibody and anticoagulation interventionsFrequent sequential analyses and pre-specified stopping rules for effectiveness, superiority, futility and inferiority in each domainBayesian hierarchical modelling to allow information sharing across pre-specified patient groupsResponse adaptive randomisation to allow increased allocation to better performing treatment arms within each domain during the course of the trial. Randomisation occurs within a centralised platform database (Spinnaker), with site investigators enrolling patients sequentially at participating hospitalsPotential to extend trial duration indefinitely provided appropriate clinical questions persist and funding support is available

The protocol documents for ASCOT ADAPT consist of an overarching core protocol, a statistical appendix, a domain specific appendix (DSA) for each domain and region-specific appendices (RSA) (Fig. 1). The protocol is designed to minimise the need for core amendments or ethical review with trial adaptations (for example, the addition of interventions within a domain, or of entire domains). Trial documents, including core and domain protocols and statistical appendices, are available at https://www.ascot-trial.edu.au/pages/resources

**Fig. 1 Fig1:**
[figure not shown]
Patient flow if eligible for platform entry

ASCOT ADAPT commenced with three domains, with the potential to add more domains in the future. In theory, an unlimited number of domains are possible but must be balanced by pragmatic restrictions on trial size and conduct. These are antiviral, therapeutic antibody and anticoagulation domains (Fig. 2). An important aspect of the pragmatic design of ASCOT ADAPT is the recognition that “standard of care” for COVID-19 will evolve during the life of the platform and that patients enrolled in ASCOT-ADAPT will be allowed to receive standard of care interventions in addition to allocated trial interventions, as long as there is no biological interaction or contraindication with an active domain. In other words, ASCOT ADAPT is testing the effect of the addition of selected interventions to the current standard of care, seeking an incremental benefit. At the time of writing, standard of care for severe COVID-19 in Australia includes low-dose thromboprophylaxis, dexamethasone, remdesivir (if on supplemental oxygen but not mechanically ventilated), and one of baricitinib, tocilizumab, or sarilumab [14].

**Fig. 2 Fig2:**
[figure not shown]
Three domains of ASCOT ADAPT

ASCOT ADAPT discourages the use of therapies which have not clearly been shown to provide clinical benefit but does not exclude participants from enrolment if they have been administered. Initial domains and interventions are described in detail below, and new interventions can be added to them and other domains if and when they become available and are assessed as meeting criteria to enter the platform. To be added to the platform, a candidate intervention is first assessed by the ASCOT ADAPT therapeutics advisory committee, who may seek further information and can then recommend an intervention to the global trial steering committee for addition to the platform. In general, to be added to the platform, an intervention needs to have sufficient human safety data, a strong biological plausibility for activity against SARS-CoV-2 or the associated host response and have preliminary human efficacy data. In addition, ASCOT ADAPT will prioritise interventions which are available and affordable.

The overall aim of the ASCOT ADAPT study is to evaluate potential therapeutics in adults hospitalised with SARS-CoV-2 infection, for reducing all-cause mortality or progression to intensive care level support within 28 days of randomisation. The key elements of the trial design are summarised in Table 1. The SPIRIT checklist is attached as Additional file 1 [15]. Figure 3 shows key governance structures overseeing the trial implementation and conduct.

**Table 1 Tab1:** Key trial design elements for ASCOT ADAPT

Core primary outcome measure	Death from any cause or requirement of new intensive respiratory support (invasive or non-invasive ventilation) or vasopressor/inotropic support in the 28 days after randomisation
**Core secondary outcome measures**	1. Time to clinical recovery during the first 28 days after randomisation 2. WHO 8-point ordinal outcome scale at day 28 post randomisation 3. All-cause mortality at 28 and 90 days post randomisation 4. Days alive and free of hospital by 28 days post randomisation 5. Days alive and free of ventilation by 28 days post randomisation 6. Presence of patient reported outcome of shortness of breath at days 28 and 90 post randomisation 7. Quality of life as measured by EQ5D5L questionnaire at days 28 and 90 post randomisation
**Study domains**	1. Antiviral domain 2. Therapeutic antibody domain 3. Anticoagulation domain 4. Other domain (to be determined)
**Platform inclusion criteria**	1. Age ≥ 18 years 2. Admitted to an acute-care hospital 3. Confirmed SARS-CoV-2 by nucleic acid testing in the 14 days prior to randomisation 4. Able to be randomised within 14 days of symptom onset 5. At least one symptom or sign attributable to SARS-CoV-2 infection
**Platform exclusion criteria**	1. Currently receiving acute intensive respiratory support (invasive or non-invasive ventilation) or vasopressor/inotropic support 2. Previous participation in the trial 3. Treating team deems enrolment in the study is not in the best interest of the patient 4. Death is deemed to be imminent and inevitable within the next 24 h 5. Either the patient or their primary treating clinician are not committed to active treatment

**Fig. 3 Fig3:**
[figure not shown]
Key governance structures overseeing the trial implementation and conduct

### Study sites, participants and endpoints

At the time of writing, ASCOT ADAPT is operational in centres across Australia, New Zealand and India. Sites are nominated by local investigators and selected by a process involving assessment of local capacity. Efforts have been made to ensure available sites in areas of active COVID-19 community transmission to maximise study access, but support has also been provided for establishing sites in areas with little or no COVID-19 activity in anticipation of future need. Regular investigator meetings are held by teleconference, including updates on planned and newly introduced domains and interventions, and supplemented by weekly email updates.

In all sites, participants are hospitalised adult patients with confirmed SARS-CoV-2. This participant cohort was chosen for a variety of reasons, including their high risk for progression to intensive care support and/or death, and the limited therapeutic portfolio currently available to improve disease outcomes. The primary endpoint is death from any cause or requirement of new intensive respiratory support (invasive or non-invasive ventilation) or vasopressor/inotropic support in the 28 days after randomisation. This primary endpoint was chosen to reflect objective and highly prioritised outcomes, and to align with other international studies [16]. Additional secondary endpoints were also chosen to reflect community priorities resulting from focus group meetings with a wide range of stakeholders [17].

Recruitment opened on 12 February 2021. As of 1 October 2021, 1075 participants had been enrolled.

The ASCOT ADAPT trial is registered with the Australian and New Zealand Clinical Trials Registry (ACTRN12620000445976) and ClinicalTrials.gov (NCT04483960).

### Domains and interventions

ASCOT ADAPT began with antiviral, antibody, and anticoagulant domains.

*The antiviral domain* was planned to start by comparing interferon-β, interferon-β plus ribavirin, nafamostat and standard of care arms. The interferon arms were based on biological plausibility, an in vitro effect against SARS CoV-2 and clinical trial data among patients with COVID-19 from Hong Kong [18]. However, when the WHO Solidarity trial reported that interferon had no effect on the course of COVID-19, the decision was made by the Trial Steering Committee (TSC) in consultation with the Data Safety and Monitoring Committee (DSMC) to drop these arms and focus on nafamostat [11].

Nafamostat is a serine protease inhibitor. It inhibits TMPRSS2, the serine protease that primes the spike protein as part of SARS-COV-2 entry into human cells [19]. It is also an antifibrinolytic agent with weak anticoagulant properties used for prevention of coagulation of perfused blood during extracorporeal blood circulation for dialysis and is licensed in Japan and Korea for this indication and for pancreatitis. The antifibrinolytic properties of nafamostat mean that it has been used in the treatment of disseminated intravascular coagulation (DIC)—a further potential advantage of this drug as DIC can be a complication of COVID-19 [20]—and in the maintenance of cardiopulmonary bypass in patients with recent intracerebral haemorrhage [21].

Nafamostat has potent anti-SARS-CoV-2 activity in a human epithelial cell line CALU-3 [22]. The EC50 is 5-10 nM and estimated EC90 of 47nM (extrapolated from Hoffman et al). This potency exceeds that of almost all other compounds being tested as potential antiviral therapies against SARS-CoV-2, including remdesivir, making it a highly attractive compound to study. Very few drugs have low nanomolar EC50 values.

Nafamostat has moderate volume of distribution ~5 L and protein binding of 67%. Although specific data are lacking, these pharmacokinetic characteristics suggest nafamostat has extensive tissue penetration and concentrations should be favourable in highly vascularised tissues like the lung. Nafamostat is hydrolysed in blood and is not metabolised by the liver and so is not likely to be a cause of hepatic enzymosis nor would hepatic dysfunction theoretically preclude use. The half-life is very short (in the order of minutes), and so nafamostat must be administered by constant intravenous infusion. A continuous infusion of 0.2 mg/kg/h is estimated to result in steady-state total drug concentrations of 170–200 nM. When accounting for protein binding, this means the steady-state concentration: EC50 ratio is 11.2–13.2 and EC90 ratio is estimated to be 1.2–1.4. Nafamostat has been used in small case series of patients hospitalised with COVID-19 and anecdotally is in common use for this indication in Japan [23], but RCT evidence of efficacy is needed [24, 25].

*The antibody domain* initially studied convalescent plasma, with the capacity to incorporate the addition of hyperimmune globulin, monoclonal antibodies or other therapeutic antibodies. At the time, convalescent plasma looked like a promising treatment for COVID-19 based on observational data [26, 27]. The USA FDA had issued an emergency use authorisation resulting in widespread uptake of use of convalescent plasma therapeutically without solid RCT evidence. The RECOVERY trial subsequently reported futility in the use of convalescent plasma in the treatment of hospitalised patients with COVID-19 [28], as has the REMAP-CAP trial among critically unwell patients admitted to ICU with COVID-19 [29]. A decision was then made by the ASCOT-ADAPT TSC and DSMC to close convalescent plasma on 4 February 2021 as an intervention after 33 patients had been randomised within the antibody domain. The domain remains suspended at the time of writing.

*The anticoagulation domain* is currently studying prophylactic dose low molecular weight heparin (LMWH), which was the standard of care treatment for hospitalised patients with COVID-19, compared with intermediate dose LMWH and with therapeutic anticoagulation. Intermediate dose LMWH is in between traditional prophylactic dosing and therapeutic anticoagulation dosing of LMWH or intravenous heparin. A previous protocol was amended to remove a prophylactic dose + aspirin arm, following results from REMAP-CAP and RECOVERY demonstrating that aspirin provided no evident clinical benefit [30]. Approximately 280 patients had been enrolled and assigned to prophylactic dose + aspirin.

The propensity of SARS-CoV-2 to cause microvascular, venous, and arterial thrombosis appears to be both part of the pathogenesis of the disease and to cause complications among patients with moderate to severe COVID-19 [31]. The multi-platform consortium of REMAP-CAP, ACTIV, and ATTACC have recently reported on a comparison between standard prophylaxis and therapeutic anticoagulation for patients with moderate and severe COVID-19 [32, 33]. They found that therapeutic anticoagulation was beneficial for patients admitted to hospital with moderate COVID-19, but not for patients in ICU requiring critical care for COVID-19. They did not evaluate intermediate dose LMWH, which as pointed out in the accompanying editorial, remains an important question to resolve [34]. The question of whether therapeutic anticoagulation is beneficial for patients such as those who will be enrolled in ASCOT ADAPT would also be important to ascertain in a low-middle income country such as India or Nepal.

### Data collection and management

In keeping with a clinical trial implemented under pandemic conditions and elevated health system pressures, a pragmatic and streamlined core dataset was developed. Data collection is conducted by trained staff at each participating site and entered into an electronic case report form. Information collected includes eligibility criteria at randomisation, baseline patient demographic and medical information (to evaluate balance of randomisation), and information to categorise patients into the a priori subgroups of interest. During the first 14 days while the patient remains in hospital, information on daily clinical parameters is collected to measure secondary outcomes and ensure protocol compliance. At 28 days post-randomisation, information on vital status is obtained. At 28 and 90 days following randomisation, quality of life is measured using the EQ5D-5L score.

### Statistical considerations

As detailed in Table 1, the core primary outcome measure is death from any cause or requirement of new intensive respiratory support (invasive or non-invasive ventilation) or vasopressor/inotropic support in the 28 days after randomisation, represented as a binary random variable. The objective of ASCOT ADAPT is to evaluate therapeutics in a generalised factorial structure (conceptualised as domains) relative to both standard of care and all other treatments within a domain. We characterise treatment efficacy in terms of a continuum from benefit to futility. Specifically, we define ‘effective’ treatments as those that lower the log-odds of the primary outcome and ‘futile’ treatments as those that reduce the log-odds by no more than -log(1.1). A superior treatment is defined as one which has a lower log-odds than all other interventions in that domain.

Bayesian logistic regression models are used to evaluate the efficacy of treatment regimens (distinct combinations of treatments across domains) with respect to the primary outcome, adjusting for region, site, age, and time since trial commencement. Sequential analyses are scheduled to occur approximately every 3rd month throughout the trial. Each analysis uses data on all participants who have 28-day outcome data available to estimate the log-odds of the primary endpoint for all randomised participants irrespective of post-randomisation events (intent-to-treat principle). To account for temporal trends, participants are grouped into sequential cohorts (4-week epochs), with the effect of time modelled as a random walk with a prior that enforces smoothing of time-effects across adjacent epochs. Bayesian inferences are made from Markov chain Monte Carlo (MCMC) draws from the joint posterior distribution of model parameters.

At each analysis, we contrast the primary estimand for each treatment arm with standard of care in its domain. If at any analysis a treatment is estimated to be:Futile with > 95% probability, it will be droppedEffective with > 99% probability, the standard of care will be droppedSuperior with > 99% probability, all other treatments in that domain will be dropped

Response adaptive randomisation is centrally implemented for dynamically allocating treatments via a secure proprietary web interface. Following each analysis, the targeted allocation probabilities (by regimen) will be updated such that they are proportional to the probability that each regimen minimises the log-odds of the outcome. Where there are more than two interventions, allocation to usual care within a domain will be fixed as the reciprocal of the number of interventions in the domain. If the domain includes only usual care and one other active intervention, then a minimum allocation probability of 1/3 will be targeted to either intervention within that domain.

Secondary analysis methods include binary, ordinal and time to event models, all of which are implemented with a Bayesian logistic model framework that is extended as required. For ordinal measures, proportional odds are assumed.

Pre-specified subgroups are defined to explore treatment effect heterogeneity and sensitivity analyses examine how model estimates vary conditional on pre-specified analysis sets (intent-to-treat, per protocol, contemporaneous reference groups), independent domain modelling, prior specification and the implications of missing data.

A complete statistical appendix is available at https://www.ascot-trial.edu.au/pages/resources.

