### Sample size

To calibrate the decision thresholds for effectiveness, futility and superiority and evaluate the operating characteristics of the trial, we implemented pre-trial Monte Carlo simulations of hypothetical trials spanning a range of scenarios. Such methods are generally more informative than conventional power calculations as the frequency of type I and type II error is determined (by simulation) using a range of treatment effects of different size within the plausible range, including no difference (to evaluate type I error). In brief, we assumed a probability of the endpoint of 0.2 in the standard care arm, no drop-outs or missing data and analyses performed after every 200 enrolments. Estimated sample sizes varied by domain according to anticipated numbers recruited into that domain based on the time the domain will be open and domain specific eligibility. We evaluated scenarios in which no treatments in any domain were more or less effective than usual care (null scenario) and scenarios in which investigational treatments were associated with an OR of the endpoint of 1.1 (harmful), 0.8 (weak effect), 0.67 (moderate effect) and 0.5 (strong effect). For the anticoagulation domain, we evaluated a scenario where intermediate dosing was equivalent to prophylactic dosing, and therapeutic anticoagulation is the investigational treatment. For each scenario, we ran 10,000 simulations.

Table 2 provides a condensed summary of the simulation results where the pre-specified adaptive algorithm and decision thresholds are calibrated to ensure the design has a likelihood of type I error (false positive) that corresponds to a frequentist *P* value of less than 0.05. In the null scenario, an arm was falsely declared to be effective in < 5% of simulations and correctly declared as futile in > 50% of simulations. A moderately effective treatment was identified correctly as effective in at least 75% of simulations. In each domain, a strongly effective treatment was identified as effective and superior in > 85% of simulations after 1000 enrolments. Harmful treatments were identified as futile in > 80% of simulations.

**Table 2 Tab2:** Summary of results of simulations indicating probabilities for arriving at platform conclusions (effectiveness or futility) in each domain with varying sample sizes and effect sizes. The probabilities for arriving at platform conclusions can be conceptualised as similar to the power of the study

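### The futility definition has its sign reversed, and the rule evidently meant does not give Table 2's futility probabilities in the two-arm domains

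*Protocol article*

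**What the plan says.** Statistical considerations gives two definitions side by side. For benefit, "we define ‘effective’ treatments as those that lower the log-odds of the primary outcome". Futile is then defined "treatments as those that reduce the log-odds by no more than -log(1.1"). An arm is dropped if futile with more than 95% probability; standard of care is dropped if an arm is effective with more than 99% probability. In a domain with usual care and one other intervention, allocation is response-adaptive and "then a minimum allocation probability of 1/3 will be targeted to either intervention within that domain".

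The Sample size section gives the simulation settings: "we assumed a probability of the endpoint of 0.2 in the standard care arm, no drop-outs or missing data and analyses performed after every 200" participants, with scenarios at no effect and at "an OR of the endpoint of 1.1 (harmful), 0.8 (weak effect), 0.67 (moderate effect) and 0.5 (strong effect"). It sums up the futility results as null arms "correctly declared as futile in > 50% of simulations", and adds: "Harmful treatments were identified as futile in > 80% of simulations". Table 2 gives futility probabilities (antiviral / anticoagulation / antibody) of 0.67 / 0.53 / 0.58 under the null, 0.89 / 0.80 / 0.83 at OR 1.1 and 0.10 / 0.07 / 0.10 at OR 0.8. The article gives no other futility margin or threshold.

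**The concern.** There are two separate faults. First, −log(1.1) is a negative number. A reduction of at most −0.095 is an increase of at least 0.095, so the printed definition makes an arm futile only if OR ≥ 1.1. A treatment with no effect would then not be futile, yet the Sample size section counts futility under the null as a correct decision.

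Second, once the sign is repaired, the rule should give Table 2's futility columns under the printed assumptions. In the two-arm domains it does not.

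This rule decides when an arm leaves the platform, and the article says its thresholds were calibrated by these simulations. Either the text does not describe the rule that was simulated, or the chance of dropping useless or harmful arms is lower than reported.

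**Working it through.** **Inputs.** Control risk 0.20, no missing data, a look every 200, true OR 1.1 / 1.0 / 0.8 / 0.67 / 0.5 (Sample size); thresholds 0.99 and 0.95, margin 1.1 (Statistical considerations); response-adaptive allocation with a 1/3 floor for two arms, and usual care at 1/3 for three arms; N = 2000, 3200 and 1600 (Table 2). The prior is not printed, so flat, N(0, 1²) and N(0, 0.5²) priors were used.

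**Rule.** With posterior mean d and SD s for the log OR, P(effective) = Φ(−d/s) and P(futile) = Φ((d + log m)/s), where m = 1.1 is the evident intention. Two-arm results come from 10,000 simulated trials per cell; three-arm results from 2,000–6,000.

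**Effective column first.** With prior SD 0.5, antiviral / antibody:

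| True OR | Simulated | Table 2 |
|---|---|---|
| 1.0 | 0.027 / 0.025 | 0.03 / 0.03 |
| 0.8 | 0.40 / 0.32 | 0.37 / 0.30 |
| 0.67 | 0.85 / 0.75 | 0.84 / 0.75 |

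Across the priors tried, antiviral gives 0.03–0.05 under the null and 0.85–0.88 at OR 0.67. The set-up is therefore close to the one behind Table 2.

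**Literal rule (OR ≥ 1.1).** Null futility is about 0.03–0.06 in the two-arm domains, and futility at OR 1.1 is 0.11–0.17. Table 2 has 0.58–0.67 and 0.83–0.89, so the literal rule was not the one simulated.

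**Intended rule (OR > 1/1.1, 95%).**

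| Domain | True OR | Table 2 | Simulated | Shortfall (points) |
|---|---|---|---|---|
| Antiviral, N = 2000 | 1.0 | 0.67 | 0.37–0.39 | 28–30 |
| Antiviral, N = 2000 | 1.1 | 0.89 | 0.67–0.68 | 21–22 |
| Antibody, N = 1600 | 1.0 | 0.58 | 0.32–0.34 | 24–26 |
| Antibody, N = 1600 | 1.1 | 0.83 | 0.59–0.61 | 22–24 |
| Anticoagulation, N = 3200 | 1.0 | 0.53 | 0.43–0.47 | 6–10 |
| Anticoagulation, N = 3200 | 1.1 | 0.80 | 0.71–0.72 | 8–9 |

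**Closed-form check, one final look, 1:1 allocation, null.** The SE of the log OR is √(2/(n × 0.16)) with n per arm.
- N = 2000: SE = √(2/160) = 0.112. Φ(0.0953/0.112 − 1.645) = Φ(−0.79) = 0.21.
- N = 1600: SE = √(2/128) = 0.125. Φ(0.0953/0.125 − 1.645) = Φ(−0.88) = 0.19.

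At N = 2000 the estimate must exceed −0.0953 + 1.645 × 0.112 = 0.089, an observed OR of about 1.09. A null arm must look somewhat harmful to be called futile. Repeated looks raise 0.21 to about 0.38, not to 0.67.

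**Sensitivity.** A Beta-posterior version gives null futility of 0.40 and 0.31. Looks every 50 raise the null figures only to 0.45 and 0.41. Changing the prior, using 1:1 allocation, or not stopping at a boundary does not close the gap. The Monte Carlo error of the stated 0.67 with 10,000 runs is √(0.67 × 0.33/10,000) ≈ 0.005.

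**What would fit.**
- Margin 1/1.2 with 95%, at OR 1.1 / 1.0 / 0.8 / 0.67. Antiviral: 0.87–0.88 / 0.63–0.65 / 0.11–0.12 / 0.02 (Table 2: 0.89 / 0.67 / 0.10 / 0.01). Antibody: 0.81–0.82 / 0.56–0.58 / 0.10–0.11 / 0.02 (0.83 / 0.58 / 0.10 / 0.01). Anticoagulation: about 0.90 / 0.72 / 0.14 / 0.03 (0.80 / 0.53 / 0.07 / 0.01), which overshoots; about 1/1.12 to 1/1.13 fits that column best.
- Margin 1/1.1 with an 85% threshold fits the two-arm null and OR 1.1 cells (0.64–0.66 / 0.86–0.87 antiviral; 0.59–0.61 / 0.82–0.83 antibody). It overshoots at OR 0.8 (0.15–0.17 against 0.10) and OR 0.67 (0.04–0.05 against 0.01).

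**The case against.** The article condenses its simulation. The prior, the joint regimen model and the details of dropping arms in a three-arm domain are left to a statistical appendix that is not shown. A simplified model that fails to match does not by itself show an error. The sign slip is also harmless to anyone who sees the intention, and no analyst would plausibly run OR ≥ 1.1.

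Much of this stands for anticoagulation. The article says only that "we evaluated a scenario where intermediate dosing was equivalent to prophylactic dosing, and therapeutic anticoagulation is the investigational treatment", and the result depends on unprinted details: adding a rule that drops an arm whose probability of being best is below 0.05 moved null futility under 1/1.1 from about 0.46 to 0.36. A gap of 6–10 points there is weak evidence.

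It does not stand for the two-arm domains. Unprinted model features would have to raise antiviral null futility from about 0.38 to 0.67 while leaving the Effective column where it is, and none of the variations tried did so. An appendix may explain the difference, but the margin, the threshold and the results are all printed in this article and do not agree.

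A reader might infer that the simulations used 1/1.2. The documents do not support that: no single margin fits all three domains, and a different threshold is not fully excluded. Nor do they support saying that all of Table 2 is unattainable, or that the trial applies the literal OR ≥ 1.1 rule.

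**Conclusion.** The concern holds in two parts. The printed definition has its sign reversed; this follows from the wording alone and is confirmed by Table 2. The evident rule, OR > 1/1.1 with more than 95% probability, falls 21–30 percentage points short of Table 2's null and OR 1.1 futility figures in the antiviral and antibody domains. Under the stated rule, the claims of more than 50% (null) and more than 80% (harmful) therefore fail in those two domains. This rests on the printed control risk, looks, thresholds, allocation floor and sample sizes, and on a simple two-arm posterior with assumed priors; the near match of the Effective column supports that model.

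The cause is not established. A margin of 1/1.2 is a possible explanation for two domains only. The anticoagulation discrepancy is small and uncertain. The simulated values here show that the statements disagree; they are not replacement entries for Table 2.

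**What to change.** Write the rule without sign ambiguity: futile if P(log OR > −log m) exceeds the threshold, that is, OR > 1/m, with m and the threshold stated. Then check the simulation code for the margin and threshold used in each domain.

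- If they differ from 1.1 and 95%, correct the definition in Statistical considerations to the rule that was simulated.
- If 1.1 and 95% stand, rerun the trial's own simulation and restate Table 2's futility columns and the two summary claims in Sample size.

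The cost is one sentence and at most one rerun of existing code. The stated futility probabilities may become less favourable.
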